
### Primary outcome

The primary outcome of this study will be the proportion of individuals attending a BSS appointment within each group. Uptake will be determined by checking the episode status of each individual included in the study 8 weeks after the distribution of the final reminder letter.

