**Methods and analysis:**

This paper describes the protocol for a randomised controlled trial which will examine the effectiveness of adding a GPs endorsement to a reminder for BSS non-participants aged 56. All screening-eligible adults who have not responded to a BSS appointment at London North West Healthcare NHS Trust within 12 months of their initial invitation will be randomised to receive either a GP-endorsed reminder letter or reminder letter without GP endorsement. The primary outcome will be the proportion of individuals screened within each group 8 weeks after the reminder. Statistical comparisons will be made using univariate and multivariate logistic regression, with ‘uptake’ as the outcome variable, GP reminder group as the exposure and sociodemographic variables as covariates.

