### Data processing and data collection

Identification: Adults will be identified by NHS Digital only if they are registered with a consenting GP practice. Identification of eligible participants will take place using data contained within the Bowel Cancer Screening System which provides an up-to-date electronic record of uptake data for individuals enrolled in the national BSS.Data cleanse: NHS Digital will query the data of non-participants to identify type 2 opt-outs. Using the cleansed dataset, the first 1200 individuals will be selected to be included in the RCT database.Randomisation: NHS Digital will randomise eligible participants using the prerandomised dataset. The database will be split into two separate files with an equal number of people in each document using the study groups.Intervention: NHS Digital will share the data associated with each mail-out for the intervention and the control group with the mailing company called CFH Docmail Limited. CFH Docmail is an NHS Information Governance toolkit accredited mailing company that will be facilitating the mail merge throughout the study. The dataset will include study group, unique ID, personal contact details, NHS number and the practice name (only for intervention group). Reminders will be produced by merging each study group database with the reminder letter templates. The full package will include: the reminder letter, standard information booklet and a freepost return envelope. This process of sending previous non-participants a reminder 12 months after their initial invitation will continue until the study sample size (n=1200) is reached. We plan to send out 150 letters per week and send out all the reminders in 8 weeks.Data generation: once letters are sent, we will allow 8 weeks for all individuals to respond to the self-referral reminder. At the 16th week of the trial, NHS Digital will query the screening episode status of all individuals using their NHS numbers. If previous non-responders did not respond, their status will not change, and they will remain ‘non-responders’. If people confirmed and attended their appointment, they will be coded as ‘attended’. If people contacted the centre and cancelled their appointment and did not book another appointment, they will be considered ‘decliners’. If someone confirmed an appointment but did not attend, they will be coded as ‘non-attenders’. We will also request a separate category for those who have contacted the screening centre, had the initial confirmation and attended the clinic but not eligible to have the full investigation. People will be adequately screened, if they have had the full bowel scope investigation and received a definitive clinical result. For this purpose, we will additionally request the screening outcome of those who had the screening, and also information about the follow-up colonoscopy investigations. As a result, we will be able to distinguish between: (1) those who reacted to the self-referral reminders (responders) versus those who did not (non-responders), (2) those who successfully attended screening (attenders) versus those who did not (non-attenders) and (3) those who were adequately screened versus those who were not. In addition, NHS Digital will provide the Index of Multiple Deprivation (IMD) scores, using the postcodes of each individual included in the study.Data extraction: At the end of the study, after all data have been collated, the study database will be duplicated by NHS Digital. One copy will be anonymised for analysis by the University College London (UCL) research team. In the anonymisation process, all identifiable information including NHS number, full name, address, GP code and GP name will be excluded.Data deletion: Once the anonymised dataset is sent to the research team at UCL and verified, the research team will ask CFH Docmail to destroy all the datasets that were shared by NHS Digital. Only the research team at UCL will have access to the final dataset.

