### Statistical analysis

The primary outcome will be analysed to test for a significant difference in uptake between the two groups using univariate and multivariate logistic regression, with ‘adequately screened’ as the outcome measure, ‘trial arm’ as the exposure and ‘gender’ and IMD as the covariates. Secondary analyses will look at whether there are differences in sociodemographic characteristics of non-responders, decliners and non-attenders. Sample characteristics will be reported using descriptive statistics. The comparison of overall uptake between trial arms will be presented using ORs and 95% CIs.

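### The primary outcome is declared as attendance, but the primary model analyses adequate screening, which the protocol defines separately and more narrowly

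*Protocol article*

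**What the plan says.** The Primary outcome section of the protocol article declares: "The primary outcome of this study will be the proportion of individuals attending a BSS appointment within each group". It adds that uptake will be read from each person's episode status.

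The Statistical analysis section opens with "The primary outcome will be analysed to test for a significant difference in uptake between the two groups", by univariate and multivariate logistic regression, "with ‘adequately screened’ as the outcome measure". Trial arm is the exposure; gender and deprivation score are the covariates.

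The section on data processing and data collection keeps the two states apart:

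- A person who confirmed and kept the appointment is coded as attended.
- Adequate screening has its own, stricter definition: "People will be adequately screened, if they have had the full bowel scope investigation and received a definitive clinical result".
- A separate category is requested for people who "attended the clinic but not eligible to have the full investigation".
- The list of distinctions the data will support separates "those who successfully attended screening (attenders) versus those who did not (non-attenders) and (3) those who were adequately screened versus those who were not".

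The abstract (Methods and analysis) says: "The primary outcome will be the proportion of individuals screened within each group 8 weeks after the reminder". It names uptake as the model's outcome variable.

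**The concern.** The dependent variable of the primary model is not the outcome declared as primary. Two people with the same record could be scored differently depending on which section the analyst follows: someone coded as having attended, but without a full examination or a definitive result, is an event under the outcome section and a non-event under the analysis section.

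The primary endpoint carries the trial's single confirmatory claim. Both variables will be in the dataset, and the text supports calling either one primary. If their results fell on different sides of the 5% level, either could be presented as pre-specified, and a reader could not tell from the protocol whether the choice was made before or after the data were seen.

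**Working it through.** **1. Could these be two names for one variable?** The places, side by side:

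| Place in the protocol article | Term used | What it requires |
|---|---|---|
| Abstract, Methods and analysis | screened; uptake | not defined |
| Data processing, coding of status | attended | appointment confirmed and kept |
| Data processing, adequacy | adequately screened | full examination and definitive result |
| Sample size calculation | uptake; rate of response | not defined |
| Primary outcome | attending; uptake | read from episode status |
| Statistical analysis | uptake; adequately screened | as defined under data processing |

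The data collection section gives two definitions, numbers them as separate distinctions, and provides for people who come to the clinic without having the full examination. They are not synonyms. Uptake does not bridge them: the outcome section links it to attendance and the analysis section to adequate screening.

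**2. Is the boundary between them settled?** Not fully. People ineligible for the full examination get a category of their own, and the attendance distinction speaks of successful attendance. The text does not say whether this group counts as attended. Nor does it say whether someone referred for colonoscopy already has a definitive result from the bowel scope, or has one only after the colonoscopy. Status is queried once, at week 16. Letters go out over 8 weeks, so the last recipients have about 16 − 8 = 8 weeks of follow-up.

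**3. What could the difference amount to?** (Illustration.)

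Inputs from the Sample size calculation section: 10% and 15%, 600 per arm, two-sided 5%. Assumptions not in the document: these rates are attendance rates, and a fraction r of attenders in each arm is adequately screened, with r from 0.85 to 0.98.

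Formula (pooled variance under the null): power = Φ{[d√n − 1.96√(2p̄(1−p̄))] / √(p₁(1−p₁)+p₂(1−p₂))}, where d = p₂ − p₁ and p̄ is the mean of the two rates.

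The plan's own figure first. With p₁ = 0.10, p₂ = 0.15, n = 600:

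- d√n = 0.05 × 24.495 = 1.2247
- 1.96√(2 × 0.125 × 0.875) = 0.9167
- √(0.09 + 0.1275) = 0.4664
- Power = Φ(0.3081/0.4664) = Φ(0.661) = 74.6%

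The stated 80% is not reproduced; the same method needs 686 per arm. That gap exists whichever endpoint is used and is a separate sample-size matter.

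With both rates multiplied by r:

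| r (assumed) | Rates | Power at 600 per arm |
|---|---|---|
| 1.00 | 10.0% v 15.0% | 74.6% |
| 0.98 | 9.8% v 14.7% | 73.6% |
| 0.95 | 9.5% v 14.25% | 72.1% |
| 0.90 | 9.0% v 13.5% | 69.4% |
| 0.85 | 8.5% v 12.75% | 66.6% |

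In people: attendance would give 0.10 × 600 + 0.15 × 600 = 60 + 90 = 150 events. Between 2% and 15% of these, about 3 to 22 people, would be scored differently. If r is equal in both arms, the odds ratio barely moves: (0.15/0.85)/(0.10/0.90) = 1.59 for attendance, and (0.1275/0.8725)/(0.085/0.915) = 1.57 at r = 0.85. The choice would mainly change event counts and precision.

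**The case against.** **The endpoints are nested and probably close.** Adequately screened people are essentially a subset of those who come to the clinic, and the effect estimates should be similar. This stands and limits the practical effect. It does not remove the contradiction, because a handful of reclassified people can matter when a result is borderline.

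**The analysis plan may settle it.** An article may leave detail to a fuller document. Here, though, nothing has been left out: two adjacent sections state incompatible definitions, and an analysis plan could follow one only by departing from the other.

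**Attendance is not self-evidently the right choice.** A reader might infer that the letter can act only on attendance, so that adequate screening is the wrong endpoint. The documents do not support this. A letter that raises attendance also raises completed examinations, and completed screening is a legitimate outcome for a screening programme. The abstract's wording is arguably nearer to adequate screening, and the Statistical analysis section is the only place that names the model's dependent variable in defined terms.

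**Pending colonoscopies.** A reader might infer that people awaiting colonoscopy at week 16 will be scored as failures. The protocol requests colonoscopy data in connection with adequacy, so the question is fair, but it never says that the colonoscopy result is needed for a definitive result. They might be counted as not adequately screened; no more can be said.

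**Power.** A reader might infer a demonstrated loss of power. The fraction r is assumed, and the 10% and 15% are described both as uptake and as response. If they already describe people screened, there is no loss.

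**Conclusion.** The point holds as a contradiction in the current text: the declared primary outcome and the dependent variable of the primary analysis are different, separately defined variables, and no other section reconciles them. This conclusion rests on the wording alone and needs no numerical assumption.

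The size of the consequence is unknown. Under the stated assumptions, power at 600 per arm would be 66.6–73.6% rather than 74.6%. The fall from the stated 80% to 74.6% is not caused by this conflict.

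Two further inferences go beyond the text. It does not establish that attended includes people found ineligible for the full examination; that group is simply unclassified. Nor does anything show an intention to report selectively; the wording leaves that choice open. The point should still be corrected, because it concerns the primary endpoint.

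**What to change.** Use one primary endpoint in the abstract, the Primary outcome section and the Statistical analysis section.

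- **Simplest choice:** keep the declared outcome. Make attendance at a BSS appointment the dependent variable of the primary logistic model, and make adequate screening a named secondary outcome analysed with the same model.
- **Equally consistent:** make adequate screening primary throughout, provided the Primary outcome section is changed to match, with attendance as the named secondary outcome.

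In either case:

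1. Define uptake once, as the chosen primary endpoint, and use it in that sense only.
2. State in the data collection and Primary outcome sections whether people who came to the clinic but were ineligible for the full examination count as events.
3. For adequate screening, state how people whose colonoscopy result is still pending at the week-16 query are classified.
4. State which endpoint the 10% and 15% in the sample size calculation describe.

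The cost is wording only: both variables are already requested from NHS Digital. The change should be made and dated before outcome data are seen.

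### The abstract and the methods give the primary outcome different follow-up windows, and attendance is read on the date the last batch's response period ends

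*Protocol article*

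**What the plan says.** The abstract (Methods and analysis) states: "The primary outcome will be the proportion of individuals screened within each group 8 weeks after the reminder". Read plainly, that is 8 weeks from each person's own letter.

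The Primary outcome section counts "the proportion of individuals attending a BSS appointment within each group" and fixes the timing by "checking the episode status of each individual included in the study 8 weeks after the distribution of the final reminder letter". That is a single calendar date for the whole trial.

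The section Data processing and data collection gives the schedule:

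- Mailing: "We plan to send out 150 letters per week and send out all the reminders in 8 weeks". It "will continue until the study sample size (n=1200) is reached".
- Waiting period: "once letters are sent, we will allow 8 weeks for all individuals to respond to the self-referral reminder".
- Outcome reading: "At the 16th week of the trial, NHS Digital will query the screening episode status of all individuals using their NHS numbers".
- Coding: "If someone confirmed an appointment but did not attend, they will be coded as" non-attenders. The other codes are non-responder, attended, decliner (cancelled and did not rebook), and attended but not eligible for the full investigation.

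The Statistical analysis section uses adequate screening as the outcome in the regression. Data processing and data collection defines this as a full investigation with a definitive result.

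**The concern.** Two things do not fit together.

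First, the primary endpoint has two windows. One runs a fixed 8 weeks from the individual's letter. The other runs from the individual's letter to a common date, so its length depends on the mailing week. A reader, or the team at data extraction, could follow either and get a different uptake.

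Second, a period meant for responding is used as a period for attending. Responding means returning a slip or telephoning; an appointment then has to be arranged and kept. Success under either definition (attended, or adequately screened) needs the later event. For the last batch, the end of the response period and the reading of attendance fall on the same date.

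At stake are the meaning of the reported uptake, the number of events behind the comparison, and the secondary analysis of non-responders, decliners and non-attenders, whose categories have no stated place for an appointment that has not yet taken place.

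**Working it through.** **Inputs.** From Data processing and data collection: 1200 people, 150 letters a week, 8 weeks allowed, query at week 16. From Sample size calculation: 10% v 15%, two-sided 5%, 600 per arm.

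**Step 1: the schedule reproduces.** 1200 / 150 = 8 weekly batches; 8 weeks of mailing + 8 weeks = week 16. So Data processing and data collection agrees with Primary outcome, provided mailing does not overrun.

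**Step 2: follow-up by batch.** With the query 8 weeks after the last batch, batch b (b = 1 to 8) has (8 − b) + 8 = 16 − b weeks:

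| Batch | 1 | 2 | 3 | 4 | 5 | 6 | 7 | 8 |
|---|---|---|---|---|---|---|---|---|
| Weeks | 15 | 14 | 13 | 12 | 11 | 10 | 9 | 8 |

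The mean is 92 / 8 = 11.5 weeks. Seven batches exceed 8 weeks: 7 × 150 = 1050 people, or 1050 / 1200 = 87.5%. If letters go out at the start of each week and the query is made at the end of week 16, the range is 16 down to 9 weeks.

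**Step 3: time left to attend.** Someone in batch b who responds r weeks after the letter must be seen within 16 − b − r weeks to count. For a response at r = 6, that is 9 weeks in batch 1 and 2 weeks in batch 8. For a response at r = 8, still inside the allowed period, it is 7 weeks in batch 1 and none in batch 8.

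**Step 4: what this could do to power.** The documents give no delay from letter to attendance, so this step is an assumption. Let f be the share of eventual attendances captured by the query, equal in both arms, and take 10% and 15% as eventual rates. The observed rates are then p1 = 0.10f and p2 = 0.15f, with mean p. With n = 600 per arm,

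power = Φ{ [ (p2 − p1)√n − 1.96 √(2p(1 − p)) ] / √( p1(1 − p1) + p2(1 − p2) ) }.

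For f = 1: (0.05 × 24.495 − 1.96 × 0.4677) / 0.4664 = 0.66, so power is 74.6%. This is below the stated 80% before any truncation; that is a separate matter of the sample size and not part of this point.

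| f | Rates | Power | Odds ratio |
|---|---|---|---|
| 1.0 | 10% v 15% | 74.6% | 1.59 |
| 0.9 | 9% v 13.5% | 69.4% | 1.58 |
| 0.8 | 8% v 12% | 63.7% | 1.57 |
| 0.7 | 7% v 10.5% | 57.4% | 1.56 |

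**Step 5: which values of f go with which delays.** As an illustration only, take an exponential response time with a mean of 1.5 to 3.5 weeks, plus a uniform booking-to-appointment lag of 2–6 or 3–8 weeks. The first batch then captures 93–100% of eventual attenders, the last 47–91%, and the average over batches is 76–98%. Power is 61–73%. The longer lag produces the lowest values.

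**The case against.** The operational text is coherent. Data processing and data collection and Primary outcome describe the same single reading; only the abstract's short phrase differs. A common census date with a minimum of 8 weeks is a legitimate choice, and it captures more attendance than a strict 8-week cut would. This stands, and it makes the first part of the point one of reconciling definitions. It does not answer the second part: the response period and the attendance reading still coincide for the last batch.

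A reader might infer that unequal follow-up biases the comparison between arms. The documents do not support that. Individuals are randomised 1:1, both letters are planned over the same weeks, and they differ by one statement with the same booking routes. Nothing suggests that one letter leads to slower booking. Under equal truncation the odds ratio barely moves (1.59 to about 1.56).

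A reader might also infer that future bookings will be coded as non-attenders. No sentence says so, and an appointment that has not happened fits that wording poorly. Eligibility criteria mentions an open episode status for postponed appointments, so the source system can mark unfinished episodes. What stands is that such people cannot meet either definition of success at the query, and that their coding is not among the categories listed.

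The power figures are conditional. Sample size calculation describes the 10% as observed in previous work; if that came from a similarly truncated window, scaling it down counts the truncation twice. Nor can it be said that the result will not compare with earlier reminder trials, since their windows are not given.

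**Conclusion.** The point holds as one about the endpoint's definition and completeness. The abstract and the methods give different windows for 1050 of 1200 people, and follow-up under the methods ranges from about 15 down to 8 weeks. Followed exactly, the plan cannot count people in late batches who book within the allowed time and are seen after week 16, so uptake is undercounted in both arms if any such people exist.

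The loss of power is plausible but of unknown size. From 75%, it falls to about 69%, 64% or 57% if 90%, 80% or 70% of attendances are captured, assuming equal capture in both arms and that 10% and 15% are eventual rates. No bias between arms is shown, and misclassification of pending bookings as non-attenders remains an inference. If mailing runs beyond 8 weeks, week 16 and 8 weeks after the final letter also cease to be the same date, and the range of follow-up widens.

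This should be fixed; nothing here shows the primary comparison to be invalid.

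**What to change.** - Define uptake as attendance (or adequate screening, whichever is made primary) within one fixed number of weeks from each person's own mailing date. Make it the same for all batches and long enough to include appointments booked during the 8-week response period.
- Run the NHS Digital query once the last batch has completed that window, tied to the actual final mailing date and not to week 16.
- Obtain mailing week and attendance date for each person, so that the window can be applied individually.
- At any query, code a future appointment as pending, separately from non-attenders.
- State the same definition in the abstract, Data processing and data collection, and Primary outcome.

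The cost is a final extract some weeks later and a few extra date fields, with no further contact with participants. Because the analysis file is an anonymised release from NHS Digital, the added dates may need a check against the data-release approvals. It is best settled before the extract is specified.

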### Statistical analysis

The primary outcome will be analysed to test for a significant difference in uptake between the two groups using univariate and multivariate logistic regression, with ‘adequately screened’ as the outcome measure, ‘trial arm’ as the exposure and ‘gender’ and IMD as the covariates. Secondary analyses will look at whether there are differences in sociodemographic characteristics of non-responders, decliners and non-attenders. Sample characteristics will be reported using descriptive statistics. The comparison of overall uptake between trial arms will be presented using ORs and 95% CIs.

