**Trial registration number:**

ISRCTN82867861

Strengths and limitations of the studyIf effective, this study will provide a cost-effective means to promote uptake of flexible sigmoidoscopy (FS) screening in an organised programme.The key importance of this randomised controlled trial protocol is that it highlights a methodology for delivering general practitioner (GP)-endorsed reminders to examine whether a 12 months’ reminder letter can be further enhanced to improve screening uptake in an organised FS-based screening programme for colorectal cancer.There is a strong public health mandate to develop system-friendly interventions to promote uptake of the bowel scope screening programme in England, particularly among socioeconomically deprived groups, where the potential for improving uptake is greatest.The study population is limited to the patients who are registered at the participating GP practices in London Boroughs of Hillingdon, Harrow and Brent.

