## Aims

The primary aim of this RCT will be to test whether adding a GP endorsement to the 12 months’ reminder letter improves the uptake of BSS among previous non-responders over and above a 12-month reminder letter without a GP endorsement. The secondary aim will be to examine demographic differences in uptake in response to the GP-endorsed reminder letter and the standard annual reminder letter (ie, a reminder without a GP endorsement).

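### The secondary aim asks about demographic differences in uptake under each letter, but no stated analysis reports those differences by letter

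*Protocol article*

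**What the plan says.** The Aims section of the protocol article states: "The secondary aim will be to examine demographic differences in uptake in response to the GP-endorsed reminder letter and the standard annual reminder letter". That aim has three elements: uptake, demographic group and letter.

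The Statistical analysis section contains the following on this subject:

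- The primary model is a logistic regression of adequate screening, with "trial arm’ as the exposure and ‘gender’ and IMD as the covariates". No arm-by-covariate term and no arm-specific model is mentioned.
- The secondary work is one sentence: "Secondary analyses will look at whether there are differences in sociodemographic characteristics of non-responders, decliners and non-attenders".
- The reported contrast is an overall one: "The comparison of overall uptake between trial arms will be presented using ORs and 95% CIs".

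The Data processing and data collection section defines the three categories named in the secondary analysis:

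- On the first category it says: "If previous non-responders did not respond, their status will not change, and they will remain ‘non-responders".
- On the second it says: "If people contacted the centre and cancelled their appointment and did not book another appointment, they will be considered ‘decliners".
- The third, non-attenders, is the code for people who had a confirmed appointment and then failed to come.

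The strengths and limitations list refers to a public health mandate to raise uptake, "particularly among socioeconomically deprived groups, where the potential for improving uptake is greatest".

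**The concern.** The declared secondary aim and the declared secondary analysis do not match. The aim needs uptake described by demographic group under each letter. The analysis sentence describes the sociodemographic make-up of three outcome categories and says nothing about which letter people received. The primary model does use both arm and demographics, but as separate covariates, so it yields one odds ratio for the endorsement that applies to men and women and at every level of deprivation.

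If the plan is followed as written, the report could say whether men or people in deprived areas were screened less often overall. It could not say from the data whether those gaps look different under the endorsed letter and the standard one. If such an analysis is added after results are seen, the choice of IMD form, cut-points and contrast will be open to influence from the data. The article itself points to deprived groups as having the most to gain, so readers will look for this result.

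**Working it through.** **Aim against analyses.** Each stated analysis can be checked for the three elements of the aim.

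| Analysis stated | Uptake | Demographics | By letter |
|---|---|---|---|
| Primary model, arm effect | yes | adjusted for | overall only |
| Primary model, gender and IMD effects | yes | yes | no, pooled over arms |
| Secondary profile of three categories | not on the coding definitions | yes | no, arm not named |

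No row has all three. Predicted uptake by arm within gender or IMD could be computed from the primary model. With main effects only, however, the arm odds ratio is the same in every group by construction, so any difference between groups in the risk difference would come from the model's form and not from an estimate.

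**What the three categories contain.** On the coding definitions, non-responders, decliners and non-attenders were all not screened. Using the rates and size in the Sample size calculation section (10% and 15%, 600 per arm):

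- expected screened: 600 × 0.10 + 600 × 0.15 = 60 + 90 = 150;
- expected not screened: 600 × 0.90 + 600 × 0.85 = 540 + 510 = 1,050.

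On those definitions the three categories lie within the 1,050, where uptake does not vary.

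**How precise a by-letter analysis would be.** The plan gives no figure for the secondary aim, so there is none to reproduce. The inputs below are its 600 per arm, 10% and 15%. (The 600 does not itself reproduce: the usual two-sided formula gives 686 per arm for 80% power. That is a separate matter and does not bear on this point.) Assume two equal subgroups, hence 300 per cell, with the same rates in each.

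- Variance terms: 0.10 × 0.90 = 0.09 and 0.15 × 0.85 = 0.1275; sum 0.2175.
- SE of the overall risk difference: √(0.2175/600) = 0.0190.
- SE within one half: √(0.2175/300) = 0.0269.
- SE of the difference between halves: √2 × 0.0269 = 0.0381, that is 3.8 points.
- 95% CI half-width: 1.96 × 3.81 = 7.5 points.
- Difference detectable with 80% power, two-sided 5%: (1.96 + 0.84) × 0.0381 = 0.107, that is 10.7 points.

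On the odds-ratio scale:

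- SE of the log ratio of odds ratios: √[2 × (1/(300 × 0.09) + 1/(300 × 0.1275))] = 0.355.
- Detectable ratio of odds ratios: exp(2.80 × 0.355) = 2.7. With an assumed 20/80 split it is about 3.5.
- If endorsed uptake were 12.5% in one half and 17.5% in the other, with 10% under the standard letter in both, the ratio of odds ratios would be 1.48 and the power of the interaction test about 20%.

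For IMD quintiles, assumed equal at 120 per arm, each cell would hold about 12 or 18 screened people. The 95% interval for a quintile's risk difference would be 1.96 × √(0.2175/120) = ±8.3 points.

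**The case against.** The strongest reply is that this is a short journal article, and that interaction terms, subgroup tables and the categorisation of IMD usually sit in a fuller plan. That would excuse silence. Here the article states a particular secondary aim and a particular secondary analysis, and the two do not correspond. The mismatch is within the document.

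Four stronger readings are tempting, and the document does not support them.

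- A reader might infer that the secondary aim is not estimated at all. The primary model does estimate gender and IMD differences in uptake among everyone sent a letter, so the aim is partly served. The by-letter part is missing.
- A reader might infer that the aim is a formal test of effect modification. The Aims section never mentions interaction and can be read as describing demographic differences within each arm. Neither reading is met, because the secondary analysis does not name arm.
- A reader might infer that people who attended are certainly left out. The comparator is not stated, and the Data processing section also uses non-attenders in a wider sense, as the counterpart of attenders. Exclusion of attenders is likely on the coding definitions but not certain. Trial arm would be absent on either sense.
- A reader might object that the profile conditions on a post-randomisation outcome. That criticism applies when an arm effect is estimated within an outcome-defined subset. This profile estimates no arm effect and is legitimate description.

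It is also fair to say that the mandate concerning deprived groups is not a hypothesis that endorsement works differently by deprivation, and that a by-letter analysis would be imprecise. Both stand. They are reasons to label the analysis exploratory, not to leave a declared aim without one.

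**Conclusion.** The point holds in limited form. The secondary aim concerns demographic differences in uptake under each letter. The stated analyses give such differences only pooled over letters, plus a profile of outcome categories that does not refer to arm. No stated analysis estimates how the differences vary by letter.

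The primary comparison is untouched. The consequence is that a declared aim has no matching by-letter analysis, or acquires one only after the data are seen. The detectable difference in effects of about 10.7 points is more than twice the 5-point effect the trial was designed around, so no confirmatory claim about subgroups should be expected. That figure assumes two equal subgroups, the plan's uptake rates in both, and that those rates apply to adequate screening. Unequal splits would be less precise.

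**What to change.** Add to the Statistical analysis section an analysis labelled exploratory, with adequate screening as the outcome:

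- report uptake by arm within gender and within IMD groups, with risk differences and 95% CIs;
- add an arm-by-gender term, and separately an arm-by-IMD term, to the primary logistic model, and report each with its 95% CI;
- use IMD as a score for the interaction, and show uptake by IMD quintile descriptively, since quintile cells are small;
- keep the profile of non-responders, decliners and non-attenders as a descriptive table shown by arm, and state which sense of non-attender applies and whether attenders form a comparison column.

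The cost is a few lines of text. Arm, gender, IMD and episode status are already part of the planned data and analysis, so nothing further need be collected. The drawback is low precision. The text should say that these results are to be read as interval estimates and that a non-significant interaction is not evidence that the endorsement works equally in all groups.
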